## Abstract

**Background:**

As the population ages, the identification of preventive strategies able to delay cognitive and functional decline associated with aging represents a major challenge. To date, multidimensional approaches seem to be effective in reducing or delaying the onset of age-related diseases.

**Objectives:**

The multicentric randomized controlled trial IN-TeMPO (ItaliaN study with Tailored Multidomain interventions to Prevent functional and cognitive decline in community-dwelling Older adults, ClinicalTrials.gov ID NCT06248723), framed within the World-Wide FINGERS network, aims to verify the efficacy of guided multidomain interventions in preventing age-related cognitive and functional decline. Within this study, we will explore a comprehensive array of established and exploratory blood biomarkers of several pathologic age-related processes, including Alzheimer’s disease (AD), neurodegeneration, inflammation, senescence and sarcopenia, to stratify subject risk and assess the effect of multidomain interventions on biomarkers.

**Design and participants:**

ApoE4 status and plasma p-tau217 (AD), NfL (neurodegeneration), GFAP and IL-6 (inflammation), GDF-15 (senescence/sarcopenia) will be evaluated in all subjects (*n* = 1,662) both at the baseline and at the end of the study (12 months). Exploratory additional biomarkers will be measured at the same time points in a subgroup of 100 subjects: BDNF, ghrelin, IGF-1, irisin and redox status in plasma as markers of sarcopenia/senescence and oxidative stress, gamma-H2AX in PBMCs as marker of senescence, and amyloid beta aggregates in plasma, urine and erythrocytes as supportive markers of AD. Untargeted metabolomics analysis in plasma and untargeted volatilomics analysis in whole blood and urine will be performed to explore molecular alterations that may be associated with the pathogenesis and progression of age-related diseases in frail older adults with the aim of identifying novel potential biomarkers.

**Conclusion:**

The comprehensive clinical use of multiple laboratory biomarkers can contribute both to the early identification of trajectories of cognitive and functional decline in older adults, and to the identification of mechanisms underlying the effect of multidisciplinary interventions on age-related pathological processes.

## Introduction

### Background and aim

The aging of the population is a trend, unprecedented in human history, which affects the whole world, and Europe and Italy in particular. It has a pervasive impact on all sectors of society, including health and economy, with serious repercussions on the wellbeing of individuals, families and communities. The identification of preventive strategies to delay cognitive and functional decline associated with aging represents a major challenge that will provide healthcare systems with useful tools for the management of age-related disorders and disabilities (Livingston et al., 2024).

To date, multidimensional approaches seem to effectively reduce the social and economic burden of age-related diseases, improving the quality of life of individuals, their relatives, and societies. These approaches typically include a healthy diet, physical activity, cognitive stimulation, social activities, and the monitoring of risk factors related to cardiovascular and metabolic disorders. The Finnish Geriatric Intervention Study to Prevent Cognitive Impairment and Disability (FINGER) was the first trial to demonstrate that simultaneous lifestyle measures in five areas can improve brain health and prevent cognitive decline (Ngandu et al., 2015).

Following this seminal study, a growing number of clinical trials have been designed to further verify the feasibility and effects of multidomain interventions in preventing dementia and disability in elderly populations across various countries and settings. Currently, over 60 countries are part of this effort, coordinated within the World-Wide FINGERS (WW-FINGERS) global network for risk reduction and prevention of dementia (Kivipelto et al., 2020). These studies not only consider cognition, but focus also on the frailty syndrome, a state of increased vulnerability resulting from aging-associated decline in reserve and function.

Within the WW-FINGERS network, our group is currently conducting the multicentric ItaliaN Study with Tailored Multidomain Interventions to Prevent Functional and Cognitive Decline in community-dwelling Older adults (IN-TeMPO), a randomized controlled trial (RCT) in older people at increased risk of dementia and with mild to moderate frailty (ClinicalTrials.gov ID NCT06248723).

Only a limited number of similar studies include a comprehensive assessment of blood biomarkers to evaluate several pathologic processes which can help to predict intervention benefits and underscore their biological underpinnings (Ha and Son, 2018; Boardley et al., 2007). To address this gap, we resolved to leverage the IN-TeMPO trial to test the effect of multidomain interventions on a panel of established and exploratory blood biomarkers of Alzheimer’s disease (AD), neurodegeneration, inflammation, senescence, sarcopenia, and oxidative stress to stratify subjects´ risk and identify possible surrogate measures of the effect of multidomain interventions.

### Study population

The recruiting phase is currently ongoing within the IN-TeMPO study (ClinicalTrials.gov ID NCT06248723, protocol article in preparation), a RCT harmonized with the WW-FINGERS network, involving 9 clinical Italian centers (2 in the North, 2 in the Center, and 5 in the South). Briefly, a total of 1,662 community-dwelling older adults at increased risk of dementia and with mild to moderate frailty will be enrolled, according to the following inclusion criteria: age ≥ 60 years, Primary Care Frailty Index score between 0.07 and 0.21, Cardiovascular Risk Factors, Aging, and Dementia Risk Score (CAIDE) ≥ 6, Clinical Dementia Rating scale (CDR) ≤ 0.5, presence of an increased risk of developing dementia due to family history and/or at least one modifiable risk factor. The recruited subjects will be randomized into two groups. The first group will receive multicomponent interventions focusing on nutrition, physical exercise, cognitive training, management of metabolic and vascular risk factors, social activities, oral health, and recommendations for quality sleep. The second group will engage in self-guided interventions and will receive suggestions through app-web or video tutorials on the same domains. Wearable devices will be assigned to enrolled subjects to obtain clinical parameters. Informatic resources and artificial intelligence tools will be adopted to collect, analyze and share data. The primary objective is to evaluate the 12-month effect of multidimensional interventions on cognitive performance through a battery of neuropsychological tests (mNTB) in the active vs. the self-guided intervention group. Secondary and explorative objectives include assessing the impact of multidimensional interventions on functional and physical performance, as well as on a panel of blood biomarkers of cognitive and functional decline.

### Selection of blood biomarkers

A panel of blood biomarkers related to the main pathophysiological mechanisms underlying cognitive decline and physical frailty associated with aging will be analyzed in all subjects recruited in the IN-TeMPO study, both at the baseline and at the end of the study (12 months) (Table 1). The strategy that guided the selection of biomarkers was based primarily on expert consensus among the research team and the latest evidence from the literature on biomarkers related to In-TeMPO key outcomes [dementia and frailty (Salvioli et al., 2023)]. This selection was also driven by an adjunctive research hypothesis aimed at monitoring the pathways expected to be positively affected by the multidomain interventions. A schematic representation of all analyzed blood biomarkers and multidomain interventions planned for the IN-TeMPO study is shown in Figure 1.

**Table 1 tab1:** List of biomarkers evaluated in biological samples obtained from subjects participating in the IN-TeMPO study.

Biomarker	Specificity	Evaluated in:	Time pionts (months)	Biological sample	Sample storage temperature (°C)	Method
ApoE genotype	AD	All subjects	T0	Whole blood	-20	Real-Time PCR
p-tau217	AD	All subjects	T0, T12	Plasma	−80	CLEIA Lumipulse®
NfL	Neurodegeneration	All subjects	T0, T12	Plasma	−80	CLEIA Lumipulse®/ Simoa®
GFAP	Inflammation	All subjects	T0, T12	Plasma	−80	CLEIA Lumipulse®/ Simoa®
IL-6	Inflammation	All subjects	T0, T12	Plasma	−80	ELISA
GDF-15	Sarcopenia/senescence	All subjects	T0, T12	Plasma	−80	ELISA
γ-H2AX	Senescence	Subgroup (*n* = 100 subjects)	T0, T12	PBMCs	−80	Confocal microscopy
Redox status (NAD+/NADH, NADP+/NADPH, oxidized and reduced glutathione)	Oxidative stress/senescence	Subgroup (*n* = 100 subjects)	T0, T12	Plasma	−80	ELISA
Untargeted fingerprint	Senescence	Subgroup (*n* = 100 subjects)	T0, T12	Plasma	−80	FTIR spectroscopy
Metabolic fingerprint and profiling	Senescence	Subgroup (*n* = 100 subjects)	T0, T12	Plasma	−80	NMR spectroscopy
BDNF	Sarcopenia	Subgroup (*n* = 100 subjects)	T0, T12	Plasma	−80	ELISA
Ghrelin	Senescence/sarcopenia	Subgroup (*n* = 100 subjects)	T0, T12	Plasma	-80	ELISA
IGF-1	Senescence	Subgroup (*n* = 100 subjects)	T0, T12	Plasma	-80	ELISA
Irisin	Sarcopenia	Subgroup (*n* = 100 subjects)	T0, T12	Plasma	-80	ELISA
Untargeted volatilomics	Senescence/neurodegeneration/AD/inflammation	Subgroup (*n* = 100 subjects)	T0, T12	Whole blood, urine	−20	SPME-GC/MS, electronic nose
Protein aggregates	AD	Subgroup (*n* = 100 subjects)	T0, T12	Plasma, urine erythrocytes	−20 -80	AFM, spectrofluorimetry

The table lists all evaluated biomarkers, their specificity, the number of subjects analyzed, the time points, the type of biological sample and its storage temperature, and the method used. CLEIA, ChemiLuminescence Enzyme ImmunoAssay; Simoa, Single-molecule array; FTIR spectroscopy, Fourier-Transform Infrared Spectroscopy; NMR spectroscopy, Nuclear Magnetic Resonance spectroscopy; SPME-GC/MS, Solid-Phase MicroExtraction and Gas Chromatography/Mass Spectrometry; AFM, Atomic Force Microscopy.

**Figure 1 fig1:**
[figure not shown]
Blood biomarkers and multidomain interventions of the IN-TeMPO study.

#### Genetic risk factor

Apolipoprotein E (ApoE) genotype will be assessed in all recruited subjects at the baseline. ApoE ε4 is the most prevalent genetic risk factor for AD, increasing the likelihood of developing the disease by 2–3 times. New additional functions of ApoE on multiple amyloid beta (Aβ) -related or-independent pathways have been recognized (Raulin et al., 2022), opening the possibility of designing new effective ApoE-targeted therapeutic strategies for AD. Furthermore, multidomain interventions may be beneficial for cognition in older at-risk individuals even carrying the ApoE ε4 allele (Solomon et al., 2018; Sakurai et al., 2024; Andrieu et al., 2017; Hafdi et al., 2021) and recent studies are currently investigating whether such benefits are more pronounced in ApoE ε4 carriers compared with noncarriers (Forcano et al., 2021; Barbera et al., 2024).

#### Alzheimer’s disease continuum

Plasma phosphorylated-tau217 (p-tau217) has been selected as core blood biomarker of AD, based on its optimal performance to predict brain amyloid positivity found in the more recent literature (Ashton et al., 2023; Jack et al., 2024). Among the different p-tau isoforms, plasma p-tau217 displays the highest performance in both the early detection of AD pathology as shown by cerebrospinal fluid (CSF), showing the highest fold increase compared to the isoforms 181 and 231, and in differentiating AD from other neurodegenerative diseases in cognitively unimpaired subjects (Janelidze et al., 2023; Ashton et al., 2024). Increased p-tau217 levels are also associated with worsening brain atrophy and cognitive performance in AD patients (Ashton et al., 2022; Jonaitis et al., 2023). Furthermore, plasma p-tau217 assessment has recently been shown to predict the development of cognitive impairment up to 10 years later (Yakoub et al., 2024).

Aβ aggregates in plasma and erythrocytes will be analyzed as supportive markers of AD continuum in a subgroup of enrolled subjects (*n* = 100). Pathological protein aggregation is considered a key hallmark of a number of neurodegenerative diseases (Wilson et al., 2023). A previous study (Lan et al., 2015) and a more recent one (Nirmalraj et al., 2021) have yielded valuable preliminary insights into the clinical utility of nanoscale data gleaned from protein aggregate profiling on red blood cells (RBCs) of individuals experiencing memory issues and cognitive impairments. Through Atomic Force Microscopy (AFM) and the Thioflavin T (ThT) assay we aim to investigate the prevalence and the physical variations of AD associated-protein aggregates free in plasma or adsorbed on RBC membranes which may offer significant insights, at a systemic level, on the disease stage and progression. Moreover, as Aβ in circulating plasma is to some degree filtered into the urine of AD patients (Takata et al., 2008) we plan to implement an Aβ42 seed amplification assay (Salvadores et al., 2014) into urine samples of the same enrolled patients aiming to amplify and detect small amounts of misfolded Aβ oligomers glomerulus filtered.

#### Neurodegeneration

Neurofilament light chain (NfL), an intermediate filament with structural functions in the neuronal cytoskeleton, is a well-established biomarker of neurodegeneration. NfL levels greatly increase in both CSF and blood after axonal damage in many neurodegenerative conditions, including AD (Zetterberg et al., 2016). Albeit lacking specificity, NfL correlates with AD progression and is reported in the latest AD criteria as a biomarker of neurodegeneration (Jack et al., 2024). Interestingly, NfL levels seem to discriminate between different preclinical AD stages, such as Subjective Cognitive Decline (SCD) and Mild Cognitive Impairment (MCI) (Giacomucci et al., 2022), correlating with the disease progression; for this reason, it will be measured in all recruited subjects.

#### Neuroinflammation

Glial fibrillary acidic protein (GFAP) and interleukin-6 (IL-6) plasma levels have been chosen as inflammatory markers in the aging process.

GFAP is a class-III intermediate filament present mainly in astrocytes and involved in CNS architecture maintenance, cell communication and blood–brain barrier functioning. GFAP reflects early astrogliosis and neuroinflammation in AD, and recent evidence suggests that GFAP may increase before other well-known biomarkers (Fontana et al., 2023). Plasma GFAP levels are able to predict the risk of dementia in individuals with SCD and MCI (Ingannato et al., 2024; Wang et al., 2024), with an even better performance in plasma than in CSF (Wojdała et al., 2023; Benedet et al., 2021). However, similarly to NfL, the diagnostic value of plasma GFAP levels is strongly limited by non-specificity (Teunissen et al., 2022; Pichet Binette et al., 2023).

The pro-inflammatory cytokine IL-6, whose concentration increases in elderly subjects, is widely used as a sensor of inflammaging (Franceschi and Campisi, 2014). Together with TNF-*α*, IL-6 induces the production of C-reactive protein, another well-known age-associated inflammatory marker. Increased IL-6 levels are associated with geriatric syndromes including frailty, sarcopenia, and impaired functional capacity (Darvin et al., 2014).

#### Sarcopenia and muscle exercise

Growth/differentiation factor 15 (GDF-15) is a member of the TGF-*β* superfamily that is highly expressed in muscle tissue and will be used as a biomarker of senescence. Its expression is low in healthy, young subjects, with a range of 200–1,200 pg./mL (Breit et al., 2011). However, there is a notable increase in cases of chronic or acute disease conditions that may be age-related (Conte et al., 2019; Conte et al., 2020b). Furthermore, it is associated with a range of other conditions, including muscle atrophy, neurodegeneration, mitochondrial disease, and aging itself, which is independent of an individual’s health status (Lee et al., 2022; Liu et al., 2021). Moreover, GDF-15 has been proposed as a biomarker for sarcopenia, a clinical condition characterized by muscle atrophy and weakness (Kim et al., 2020; Herpich et al., 2021). Indeed, several studies have demonstrated a positive correlation between elevated serum levels of GDF-15 and a decline in skeletal muscle quality (Semba et al., 2020). While mounting evidence suggests a link between GDF-15 and sarcopenia, the precise function of GDF-15 in the reduction of muscle mass and function remains uncertain.

As additional biomarkers of sarcopenia and senescence, in a convenience sample of 100 enrolled subjects we will assess brain-derived neurotrophic factor (BDNF), a neurotrophin that plays a role in maintaining brain function. The concentration of BDNF varies throughout the lifespan, with generally higher levels observed during childhood than during adulthood. However, BDNF levels tend to be higher in early adulthood, with a gradual decrease observed over time (Webster et al., 2006). BDNF has also been associated with the processes of muscle repair, regeneration, and differentiation (Kalinkovich and Livshits, 2015). Importantly, BDNF plasma levels significantly increase with physical exercise, further supporting the role of exercise therapy in the prevention of cognitive decline (Coelho et al., 2014; Tsai et al., 2018). Therefore, BDNF may serve as a potential surrogate marker of sarcopenia and muscle exercise.

Another biomarker that will be evaluated in the same subgroup is ghrelin, a gastric peptide with GH-secretagogue activity that promotes the activation of the GH/IGF-1 axis, stimulates appetite and food intake, and is involved in the regulation of energy balance (Pradhan et al., 2013). It is well documented that ghrelin levels decline with age (Serra-Prat et al., 2007; Rigamonti et al., 2002). Despite the ongoing investigation into the relationship between ghrelin levels and sarcopenia, further research is required to fully establish this association (Serra-Prat et al., 2015).

We will be measuring insulin-like growth factor (IGF-1), a circulating hormone with an anabolic effect on muscle, the secretion of which declines throughout life (Chew et al., 2019). Normally, low levels of IGF-1 are associated with impaired muscle function and strength, making it potentially involved in the sarcopenic process (Roubenoff et al., 2003).

We will also study irisin, a myokine that plays an important role in energy regulation through the molecular mechanism known as “browning,” the conversion of mature adipocytes to a brown phenotype. It also improves glucose tolerance and reduces insulin resistance (Liu et al., 2022). Irisin levels are positively correlated with muscle mass and strength and tend to increase with physical training in humans and animals, while decreasing with age and under conditions of muscle atrophy and sarcopenia (Chang et al., 2017; Park et al., 2019), thus serving as a marker of the effect of muscle exercise.

#### Oxidative stress

Oxidative stress, resulting from the accumulation of reactive oxygen species (ROS) due to an imbalance between the oxidant-antioxidant systems, and energy metabolism impairment strongly contribute to cell damages associated with aging. In particular, nicotinamide adenine dinucleotide (NAD) metabolism plays an important role, not only in regulating ROS generation and antioxidant defence against oxidative stress, but also in cellular energy production. Furthermore, an altered mitochondrial respiratory activity and low levels of NAD metabolites (i.e., NAD+/NADP+) are associated to functional alterations in sarcopenic muscle. Consequently, monitoring the levels of key nicotinamide cofactors and glutathione in its reduced and oxidized forms are valuable biomarkers to assess the effectiveness of redox metabolism anti-oxidant defences.

#### Senescence

Phosphorylation of the histone variant H2AX producing *γ*-H2AX is a well-established molecular marker of double-strand breaks (DSBs), the most deleterious DNA lesions used as index of cell senescence. Indeed, quantitation of γ-H2AX foci by immunofluorescence represents a highly sensitive and specific method for the detection of these DNA lesions. The potential of γ-H2AX to act as a molecular marker in aging is emerging, and this is an area that is expected to be intensely investigated (Shreeya et al., 2023).

#### Untargeted –omics analyses of exploratory biomarkers

In addition to the study of specific biomarkers, untargeted analyses will also be performed in a subgroup of *n* = 100 enrolled subjects, aimed at identifying new biomarkers and/or specific molecular signatures related to aging. The decision to limit-omics analyses to 100 subjects is primarily based on the explorative nature of this part of the study and on the awareness that this sample size can be more than adequate to obtain robust indications on new possible biomarkers and pathways associated with aging. Furthermore, these analyses are high demanding in terms of execution times and costs, and the preparation of the biological samples necessary for these analyses is time-consuming and requires dedicated laboratory personnel not available in all recruiting clinical centers. Finally, the management and analysis of the large amount of results obtained with-omics techniques cannot be sustained in this study protocol on a larger number of subjects.

Untargeted metabolomics analysis via NMR spectroscopy will be performed in plasma, to provide both the “metabolic profiling” and the “metabolic fingerprint” of samples (Ghini et al., 2023). The metabolomic profiling is the total analysis of all metabolites assigned and quantified in samples, enabling the detection of changes in the metabolite concentrations, identifying potential biomarkers or metabolic pathways related to specific pathological conditions (Airoldi et al., 2016; Ciaramelli et al., 2017). On the other hand, the metabolomic fingerprinting relies on the analysis of spectral data, without prior signal assignment or metabolite quantitation, providing a rapid sample classification by multivariate statistical approaches, to discriminate between samples from different biological groups (i.e., before *vs* after treatment). Fingerprinting can be equated to a super-biomarker with superior discriminating power to the best single metabolite (or a group of the best metabolites). The NMR analysis of plasma metabolites has recently proven to be effective for the identification of cognitive decline and dementia markers in aged individuals (Conde et al., 2024).

Untargeted analysis of plasma will be also performed by Fourier transform infrared (FTIR) spectroscopy, which provides a snapshot of the molecular composition and structure of the investigated samples, called “spectroscopic fingerprint.” In particular, in the FTIR spectra of complex systems there is a combined and overlapping response of biomolecules, which, on one hand, prevents the identification of individual molecules but, on the other hand, allows for the simultaneous fingerprinting of different components (proteins, lipids, nucleic acids, and metabolites) (Baker et al., 2016). The spectroscopic fingerprint of plasma is expected to reflect the individual’s physio-pathological state. The application of machine learning-based methods allows for the classification of individuals based on the spectroscopic pattern and the identification of the spectral bands responsible for the classification accuracy provides information about clinical analytes. This enables the use of the spectroscopic fingerprint also for clinical phenotypes where the molecular origin is unclear (Baker et al., 2016). The potential use of IR spectroscopy, coupled with machine learning approaches, for the identification of spectroscopic biomarkers as useful diagnostic/prognostic tools has been reported (Baker et al., 2016; Paraskevaidi et al., 2017; Ami et al., 2021; Eissa et al., 2024).

Moreover, untargeted volatilomics analysis will be carried out in whole blood and urine to identify and measure those Volatile Organic Compounds (VOCs), part of the so-called human “volatilome,” that can be proposed as VOC biomarker patterns for AD and neurodegenerative diseases (González-Domínguez et al., 2017; Enche Ady et al., 2017). Volatilomics is indeed an emerging branch of metabolomics that studies biological systems as a whole identifying volatile metabolites within it for early diagnosis and exploration of mechanisms underlying a disease (Oxner et al., 2023; Hu et al., 2022). The human volatilome profile reflects biochemical processes that occur at the onset of a disease, and it can be extracted in non-invasive or semi-invasive mode from a series of biological samples (breath, urine, blood, saliva, feces, etc.) (Drabińska et al., 2021). Volatilomics-based approach for AD and neurodegenerative diseases is offering a novel tool to investigate the underlying pathologies (Conte et al., 2020a; Jiao et al., 2023; Lau et al., 2017; Tisch et al., 2013; Ubeda et al., 2022; Kimball et al., 2016; Conte et al., 2021). In this study we will use the VOC analysis in whole blood and urine to verify the effects of multidomain interventions on the sample population. The challenge is to extend basic knowledge about altered biochemical and metabolic pathways related to AD and neurodegenerative diseases, hence joining protein marker evidence in a novel integrated vision of such diseases.

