### Data analysis

Biomarkers value distribution and outliers will be checked. Logistic regression models will be used to predict AD using Lumipulse plasma p-tau217 > 0.14 pg./mL as a standard of truth, based on previously reported thresholds in Subjective Cognitive Decline ([name], [name], et al., Plasma and CSF biomarkers in Subjective Cognitive Decline: the BBRC Alzheimer at-risk (*Β*-AARC) cohort, personal communication at AD/PD™ 2025 Alzheimer’s & Parkinson’s Diseases Conference, April 1–5, Vienna). Biomarkers will first be tested individually as predictors (univariate models), and then in combination (multivariate models). Sensitivity, specificity, accuracy, and predictive values will be derived using Receiver Operating Characteristic (ROC) curve analysis. Optimal cut-offs will be determined based on the Youden index for univariate models. Differences in model performance (AUCs) will be assessed using the DeLong test. The influence of key demographic and genetic variables (age, sex, ApoE genotype) on biomarker distribution will be evaluated by including them as covariates in multivariate models. Adjusted and unadjusted models will be compared using Akaike (AIC) and Bayesian (BIC) Information Criteria.

Analyses of the main objective will include: (1) assess if baseline biomarkers levels can predict intervention response (e.g., heterogeneity of intervention effects) in order to identify biomarkers-based phenotypes/profiles with higher intervention benefits; (2) interventions effects on biomarkers levels; (3) relationship between change in biomarkers and change in clinical outcomes (cognition, frailty). Points 2 and 3 will help understand intervention effects on disease biomarkers and biological mechanisms of beneficial effects on different outcomes. Untargeted/exploratory-omics biomarkers will be analyzed with machine learning considering different predictors.

All *p*-values will be corrected for multiple comparisons using False Discovery Rate.

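### The only contrast named for the NMR fingerprint is before versus after treatment, and biological mechanism is read partly from a change-versus-change association; neither isolates the guided programme

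*Protocol article*

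**What the plan says.** Study population sets up the comparison: "The recruited subjects will be randomized into two groups", and the primary cognitive objective is assessed "in the active vs. the self-guided intervention group". Impact on biomarkers follows as a secondary or exploratory objective, with no contrast restated. The comparator is not untreated: "The second group will engage in self-guided interventions", covering the same domains as the guided arm. Under Sample collection and storage, both arms give blood at baseline and after 12 months.

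The section on untargeted –omics analyses says that NMR fingerprinting gives a rapid multivariate classification "to discriminate between samples from different biological groups (i.e., before *vs* after treatment". Arm is not mentioned. In the same section, volatilomics is to be used "to verify the effects of multidomain interventions on the sample population", with no comparator named.

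Data analysis lists three items: (1) baseline biomarkers as predictors of intervention response, (2) intervention effects on biomarker levels, and (3) the relationship between biomarker change and change in cognition or frailty. It then states: "Points 2 and 3 will help understand intervention effects on disease biomarkers and biological mechanisms of beneficial effects on different outcomes". Omics data go to machine learning with unspecified predictors, and p-values are corrected by false discovery rate.

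**The concern.** Because both arms are treated and both are sampled twice, every participant has a before and an after sample. Separating T0 from T12 samples shows that something changed over a year. It does not show that the guided programme changed it. The same section also looks for molecular signatures of ageing, and one T0-T12 contrast cannot identify both ageing and treatment.

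Point 3 has a different weakness. Both changes are measured after randomisation and at the same two visits. They can move together because of general health, intercurrent illness or anything else that affects both on the day or over the year, with no arm effect on either. False discovery rate correction limits chance findings and removes neither bias.

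At stake are the article's stated aims of finding surrogate measures of the intervention's effect and explaining how it works. A clean before/after separation or a significant change-change correlation could be reported in support of those aims without saying anything about guided versus self-guided intervention.

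**Working it through.** The article gives no figure to reproduce: no alpha, power, effect size, SD, dropout or within-person correlation. From the article come n = 100 (omics subgroup), N = 1,662, two arms, and samples at T0 and T12. Everything else is assumed: two-sided alpha 0.05, 1:1 allocation also within the subgroup (50 and 50), T0-T12 correlation r from 0.5 to 0.9, and a drift d in SD units that is equal in both arms, with zero arm effect.

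**Before/after test of one marker.** The SD of the within-person change is √(2(1 − r)). At r = 0.7 this is √0.6 = 0.775. The noncentrality is d / (0.775/√n). For d = 0.3 it is 0.3/0.1095 = 2.74 at n = 50 and 0.3/0.0775 = 3.87 at n = 100. Rejection rates from the noncentral t distribution:

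| r | drift (SD) | n = 50 (one arm) | n = 100 (arms pooled) |
|---|---|---|---|
| 0.5 | 0.1 | 11% | 17% |
| 0.5 | 0.2 | 28% | 51% |
| 0.5 | 0.3 | 55% | 84% |
| 0.7 | 0.1 | 15% | 25% |
| 0.7 | 0.2 | 43% | 73% |
| 0.7 | 0.3 | 77% | 97% |
| 0.9 | 0.1 | 34% | 60% |
| 0.9 | 0.2 | 87% | 99% |
| 0.9 | 0.3 | over 99% | about 100% |

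**Between-arm test on the same data.** A common drift cancels in the difference between arms. In 5,000 simulated trials (r = 0.7, d = 0.3, 50 per arm), the between-arm test of change rejected in 4.4% of runs, against a nominal 5%. The before/after test within the active arm rejected in 76%.

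**Change versus change.** Let each measure have unit variance and retest correlation r, and let a share v of the variance at each visit be common to biomarker and outcome. The covariance of the two changes is 2v and the variance of each change is 2(1 − r), so their correlation is v/(1 − r). With v = 0.05 and r = 0.7 this is 0.05/0.30 = 0.167. For a smaller correlation of 0.10, the Fisher statistic is atanh(0.10) × √(n − 3):

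- n = 1,662: 0.1003 × √1,659 = 4.09, significant in 98% of cases.
- n = 100: 0.1003 × √97 = 0.99, significant in about 17% of cases.

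**Cost of the between-arm contrast.** The detectable difference at 80% power with T12 adjusted for T0 is (1.960 + 0.842) × √(2/n) × √(1 − r²), with n per arm. With 50 per arm and r = 0.7 this is 2.802 × 0.200 × 0.714 = 0.40 SD (0.49 at r = 0.5, 0.24 at r = 0.9). The pooled before/after test with n = 100 and r = 0.7 would detect 2.802 × 0.0775 = 0.22 SD, but of a quantity that is not the intervention effect. With 831 per arm, as for the markers measured in everyone, the between-arm figure is about 0.10 SD at r = 0.7. Dropout is ignored throughout.

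**The case against.** The strongest reply is that the trial does plan a randomised analysis. Points 1 and 2 in Data analysis concern intervention effects. In a two-arm trial whose stated comparison is active versus self-guided, they read naturally as between-arm. That stands. A reader might infer that the article replaces the randomised comparison with before/after contrasts across the biomarker panel. The text does not support this: point 3 is listed in addition to point 2, not in its place.

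The before/after phrase also sits in a parenthesis within a description of what NMR fingerprinting does. That limits its reach. The FTIR paragraph speaks of classifying individuals, and the volatilomics paragraph names no comparator of any kind, so neither can be said to plan a before/after contrast. Still, the parenthesis is introduced as a definition and not as an example, and no other contrast is given for the fingerprint.

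Point 3 is called a relationship, and the article claims only that points 2 and 3 together help understanding; it does not claim mediation. This softens the problem, but the sentence still assigns mechanism to an association that randomisation does not protect.

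Storage time and assay batch are possible time effects for the omics contrast, not documented ones. How paired samples are batched is detail that an article may leave to the full protocol. These effects cannot explain a correlation under point 3, because they do not move cognitive scores. The calculation there needs a component shared between a plasma assay and a clinical score, and its size is unknown.

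**Conclusion.** The point holds in a limited form. The one contrast named for the NMR fingerprint confounds treatment with time, and point 3 contributes to a reading of mechanism that it cannot support alone. Points 1 and 2 are not at fault. The direction of both problems follows from the design; their size does not. The rates of 97% against 4.4%, and 98% for a correlation of 0.10, rest on assumed drift, correlations and allocation, and the table shows before/after rejection at n = 100 running from 17% to about 100% over plausible inputs. Only secondary and exploratory analyses are concerned. The primary cognitive comparison is untouched. The change is worth making because it costs almost nothing.

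**What to change.** In the NMR and volatilomics paragraphs of the untargeted –omics section, state that intervention effects are estimated between the randomised arms, using each person's T12 minus T0 difference or T12 adjusted for T0. Report before/after differences only descriptively, within arm.

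In Data analysis, specify for point 3 a model of the 12-month outcome on arm, baseline outcome, baseline biomarker and 12-month biomarker. Including arm and baseline does not remove confounding between biomarker change and outcome change, so describe the result as an association. Reserve the word mechanism for a mediation analysis with its assumptions stated and a sensitivity analysis for that confounding.

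The cost is wording, with no new samples or assays. The drawback is precision: the between-arm omics contrast in about 100 people (split by arm not stated) will look less striking than a before/after separation.
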